### Power and sample size calculation

An F-test over three groups with a medium effect-size of treatment compared to waiting list, alpha .05 and power .80 needs 159 participants. Attrition is estimated conservatively to be high at 33%. The needed number of participants is 240. We will use 3 x 80 participants.

**Figure 1 F1:**
[figure not shown]
Flow Diagram T.TIP.

To minimize missing values: (a) research assistants will use letters, text messages, telephone calls, and contacts with participants' case workers for inviting participants and for reminding them about their assessment appointments; (b) therapists are reminded by mail and in supervision to conduct their assessments, be it assessments within sessions or at T1, T2 and T6; and (c) therapists are encouraged by mail to remind and support the participant to go to the assessment appointments with the RA at T2, T6 and T12.

All the participants will receive financial compensation of twenty-five euros for every single measurement at T0, T2, T6 and T12, regardless of whether or not the participant drops out of treatment. The compensation will be paid at the planned end of participation (T6 for waiting list participants, T12 for participants in the treatment condition).

### Interventions

#### Treatment as usual (TAU)

Participants in all three conditions PE, EMDR and waiting list receive TAU, consisting of antipsychotic medication, and treatment and/or supportive counseling by therapists, caseworkers or coaches (for example, Individual Placement and Support). TAU is considered to be equal in the three conditions as a result of the randomization procedure used (see Randomization).

### Prolonged exposure (PE)

PE therapy is a psychotherapeutic approach that reduces PTSD symptom-severity by systematically exposing the subject,in both imaginary and *in vivo* ways, to previously avoided traumatic internal and external stimuli. [63].Thetrauma-related fear memory network is activated by PE and psychopathological cognitions may be changed during PE [64]. PE consists of eight sessions of 90 minutes.

In the first treatment session, a case conceptualization is made in order to plan the treatment sessions. The therapist receives information from the Interview for Traumatic Events in Childhood (ITEC) [65], an interview that is part of T0. The ITEC captures categories (for example, sexual abuse, physical abuse) of experienced traumatic events. In addition, the intensity of re-experiencing symptoms of each traumatic event is assessed. Based on the ITEC, the therapist draws up a preliminary, formatted PE case conceptualization. In the first treatment session, the therapist will discuss and complete the case conceptualization together with the patient. This results in a hierarchy of the most relevant traumatic memories in order of significance with regard to the symptoms of PTSD. A highly qualified supervisor ([name]) reviews each case conceptualization.

In the first session, the therapist will explain the treatment rationale to the participant. Imaginary PE is carried out from the second treatment session: the confrontation with avoided anxiety provoking memories, during 45 to 60 minutes per session. The participant imaginarily relives the traumatic events. The therapist prompts the participant to tell details about the memory and to relive the memories very vividly, as if it was happening here and now. The participant is instructed to reveal sensory details of the traumatic events, and to talk in the present tense and from a personal first person perspective. The therapist helps the participant to expose himself or herself to the most fearful parts of the memory, the so-called hot spots. Subjective Units of Distress (SUDs, range 0 to 100) reflecting the levels of distress are monitored during the PE sessions. Each session is recorded and stored with a voice recorder. At home the participant listens to the complete recording five days a week, scoring the SUDs prior to, during and after listening. At session three exposure *in vivo* is added. A list is made of avoided trauma related stimuli. As homework, the participant sets out to confront these situations *in vivo* (including: on the internet). Again distress levels (SUDs) prior to, during, and after *in vivo* exposure are monitored.

### Eye movement desensitization and reprocessing (EMDR)

EMDR is a psychotherapeutic approach, in which memory representations of traumatic life experiences are processed in order to change dysfunctional beliefs about self or others that originated from damaging traumatic experiences [66,67]. EMDR consist of eight sessions of 90 minutes.

As in PE, in the first treatment session a case conceptualization is made in order to plan the treatment sessions. The therapist receives information from the ITEC. The ITEC captures categories (for example, sexual abuse, physical abuse) of experienced traumatic events. In addition, the intensity of re-experiencing symptoms of each traumatic event is assessed. Based on the ITEC, the therapist draws up a preliminary, formatted EMDR case conceptualization. In the first treatment session, the therapist will discuss and complete the case conceptualization together with the patient. This results in a hierarchy of the most relevant traumatic memories in order of significance with regard to the symptoms of PTSD. A highly qualified supervisor ([name]) reviews each case conceptualization.

After acceptance, memories are subsequently processed following the Dutch translation [68,69] of the basic EMDR protocol [67]. The participant is asked to focus on the currently most distressing image of a memory in a multi-modal manner, including image, thought (an experienced negative cognition (NC) and a more healthy positive cognition (PC)), emotion, physical sensation and level of tension (SUD). Processing of the memory starts when the therapist asks the patient to hold the target image in mind while concentrating on a distracting stimulus (the finger of the therapist eliciting eye movements) for about 30 seconds. The patient reports briefly what comes to mind and is guided by the clinician to refocus on that element while focusing on the distracting stimulus. This continues until no more associations come up and the disturbance level associated with the target memory (SUD) drops to zero. Then the therapist guides the participant in installing the PC to a maximum validity, that is a Validity of Cognition (VOC) score seven. The participant identifies any residual disturbing sensations and, if present, the memory will be processed again in the same manner as described above, until the SUD is zero and the VOC PC is seven. The therapist facilitates a positive closure to the session. In the next session a re-evaluation takes place in which the participant comments on previously processed targets as a basis for further intervention.

### Early completions

A participant will be considered an early completer of treatment when (a) his or her score on the PTSD Symptoms Scale – Self Report (PSS-SR) is lower than 10 on two consecutive occasions, and if (b) the SUDs from all situations that are part of the case conceptualization are reduced to zero.

### Measurements

Subjects participate in the study for 12 months. At T0, the RA assesses baseline measurements of all primary, secondary, tertiary and quaternary variables. At T1, at midtreatment, participants in treatment conditions are assessed for their scores on the moderator and mediator variables by self-report questionnaires handed out by the therapist. At T2, the end of treatment, the RA assesses treatment outcome variables. T6 is the first follow-up measurement, and this is the starting point for treatment for the waiting list group. T12 is the 12-month follow up measurement for the PE and EMDR group.

For participants in the treatment conditions PE and EMDR some assessments are planned within sessions: PTSD symptom severity, therapy burden, harm expectancy (pre-session) and experienced harm (post-session), adverse events (pre- and post-session), credibility of treatment and memory characteristics. Note that therapists are also assessed independently from the participants for perceived and experienced treatment burden credibility and harm, before, during and after treatment.

### Instruments

#### Measurements – inclusion

The M.I.N.I.-International Neuropsychiatric Interview-Plus (M.I.N.I.-Plus) [70-72] is used as an inclusion tool. The M.I.N.I.-Plus sections for psychotic and mood disorders will be used to assess lifetime psychotic disorder or mood disorder with psychotic features at recruitment. The M.I.N.I.-Plus is a short diagnostic interview schedule that can be easily incorporated into routine clinical interviews and is well accepted by patients [73]. The M.I.N.I.-Plus may be used in research [74]; it is fit to classify psychotic and mood disorders [74,75]. According to the C.I.D.I. [70] the Kappa coefficient, sensitivity and specificity of the M.I.N.I. were good (>0.70) or very good (>0.80) for most diagnoses including psychotic and mood disorders. Inter-rater and test-retest reliability were good (>0.70). Validation against the Structured Clinical Interview for DSM-IV (SCID-P) supported the validity and reliability of the M.I.N.I. [71].

As pointed out in the section Inclusion, the original M.I.N.I. module of suicidality was used as part of the algorithm used to exclude patients.

### Measurements –effects of treatment on PTSD symptoms and safety

See Table 1, Primary outcome measurements.

The CAPS [61] is the primary outcome measure. The CAPS assesses the presence or absence of PTSD diagnosis and the frequency and intensity of the clinician's rated PTSD symptoms. The CAPS provides ratings of the frequency and intensity of each of the 17 DSM-IV–TR based PTSD symptoms on 0 to 4 Likert-type scales, thereby allowing for a maximal score of 8 for each symptom and a total-score range from 0 to 136. The CAPS is considered the gold standard to diagnose posttraumatic stress disorder as defined in the DSM-IV-TR and to establish its severity. A review of the empirical literature on psychometric properties of the CAPS [76] indicates that the CAPS has excellent reliability (>0.90), yielding consistent scores across items, raters and testing occasions. There is also strong evidence of validity: the CAPS has excellent (>0.90) convergent and discriminant validity, diagnostic utility, and sensitivity to clinical change.

The Posttraumatic Stress Symptom Scale, Self-Report (PSS-SR) [77] is administered to assess self-reported severity of PTSD symptoms [78]. The PSS-SR consists of 17 items corresponding to the 17 diagnostic DSM-IV-TR criteria of PTSD which are rated on a 3-point Likert scale, where 0 = not at all, 1 = a little bit, 2 = somewhat and 3 = very much. It yields a total score measuring symptom severity (range 0 to 51), as well as separate severity scores for re-experiencing (range 0 to 15), avoidance (range 0 to 21), and arousal (range 0 to 15). The PSS-SR is assessed before each treatment session, to assess changes in the PTSD symptoms during treatment.

There is a satisfactory internal consistency (Cronbach’s alpha = 0.91), high test–retest reliability (*r* = 0.74) and good concurrent validity (sensitivity = 62%, positive predictive power = 100%, negative predictive power = 82% [77,79]. In a sample of patients with a first-episode psychosis the screening performance of the PSS-SR was tested against CAPS interview results [80]. The data suggest that the PSS-SR can be a useful screening instrument for PTSD in this group of patients. Sensitivity was 0.83 and specificity was 0.83.

The T.TIP Adverse Events Questionnaire (T-AEQ) is a checklist that establishes treatment safety. In seven questions the patient is asked to report any self-inflicted pain or injury, suicide attempt, deliberately hurting or physically wounding another person, excessive use of alcohol, excessive use of drugs, having needed help because of a crisis and being admitted to a psychiatric hospital. The time frame is two months.

The Adverse Events session ratings assesses adverse events in the participant before and after treatment sessions (sessions two and three), for example, being suicidal, hearing voices. Participants respond on a 10-point visual analog scale (VAS;‘no, not at all’ to ‘yes, very much’) to the questions.

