### Clinical attitudes and practice

In clinical practice, trauma exposure, PTSD and their links to psychosis do not seem to get that much attention. Traumatic experiences and the diagnosis of PTSD appear to be underreported in the charts of patients with a severe mental illness or psychotic disorder [19,20]. In addition, clinicians are reluctant to address trauma histories in patients with psychosis [21,22]. They will not easily offer therapy, especially not exposure therapy, to overcome PTSD symptoms; instead, they suggest establishing trust and rapport with patients first, and giving patients a sense of mastery, before starting to explore traumatic experiences the patients might have had [23]. Many clinicians seem to fear that trauma treatment with this patient group will lead to symptom exacerbation, crisis, hospitalization, self-harm and suicidal behavior, or rapid changes in medication. They presume that before a PTSD treatment can be safely conducted, stabilizing interventions are necessary [23,24].

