## Objectives

### Primary objective –effects of treatment on PTSD symptoms and safety

In a sample of patients who receive treatment as usual (TAU) for a current diagnosis of psychosis this study examines: a) the efficacy of PE versus waiting list, and of EMDR versus waiting list, on the symptomatology of a comorbid PTSD; and b) the safety of PE versus waiting list and EMDR versus waiting list in the treatment of PTSD.

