## Discussion

This present so called ‘T.TIP trial’ has several strengths that have the potential of making the T.TIP trial a forerunning experiment.

First, it is hypothesized that the T.TIP trial will make it possible to calibrate an efficacious and efficient short screening tool for assessing PTSD in the group of patients with psychosis. Given the fact that PTSD is underdiagnosed in this patient population [19,20], an instrument that quickly, safely and accurately assesses the risk of PTSD may be a significant aid to clinical practice.

The main goal of the study is to treat PTSD in patients with psychosis. The comparison of two trauma-focused treatments to a waiting list condition will provide answers about the effectiveness of these trauma-focused treatments on PTSD symptoms. This is the first controlled study that directly assesses the effectiveness of two guideline-recommended trauma-focused treatments in this severely mentally ill population that is generally excluded from clinical trials [29]. Further, it is a large study, including enough patients to make powerful conclusions. This would be an important contribution to treatment options for people suffering from psychosis and PTSD, as PTSD symptoms negatively influence the level of functioning and quality of life in patients with psychosis [9,10]. Conceivably, reducing these symptoms will be of great personal value to patients with psychosis who suffer from the consequences of exposure to traumatic events.

What is more, the study is aimed at establishing whether these treatments can be applied safely in this patient population. This is important for the implementation of the treatments, given the fact that clinicians are often hesitant to address issues of exposure to traumatic events in this population because they fear deterioration and crisis [23,24]. Interestingly, in this aspect, we applied short-term (eight sessions) ‘basic’ manualized treatment to this population, without any pre-treatment interventions, such as emotion-regulation, skills training, or stress management. Should these standard trauma-focused treatments prove to be safe, this will strengthen their implementation in clinical practice. A strength of the study is also that it is a multi-center trial, which will enhance the internal and external validity of the interventions.

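### The designated adverse-event measures omit two of the six harms the protocol names, and the all-arm data that could show them are not assigned to the safety objective

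*Protocol article*

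**What the plan says.** The protocol article's *Primary objective* section sets out, as its second part, "the safety of PE versus waiting list and EMDR versus waiting list in the treatment of PTSD". The motive is in *Clinical attitudes and practice*, which lists what clinicians fear from trauma treatment in this group: "symptom exacerbation, crisis, hospitalization, self-harm and suicidal behavior, or rapid changes in medication". The Discussion says that clinicians hesitate "because they fear deterioration and crisis" and adds: "Should these standard trauma-focused treatments prove to be safe, this will strengthen their implementation in clinical practice".

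Table 1 has two entries in its adverse-events row, both described in the section on effects on PTSD symptoms and safety:

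- The T-AEQ: "The T.TIP Adverse Events Questionnaire (T-AEQ) is a checklist that establishes treatment safety". Its seven questions concern self-injury, suicide attempt, harming another person, excessive alcohol, excessive drugs, needing help in a crisis, and psychiatric admission.
- The session ratings. This instrument "assesses adverse events in the participant before and after treatment sessions (sessions two and three", with being suicidal and hearing voices given as examples.

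CAPS and PSS-SR are in the same table, in the PTSD row. AHRS, DRS, GPTS and BDI-II are in Table 2 as secondary outcomes. The TiC-P, also in Table 2, counts medication use so that costs can be calculated. *Analyses* specifies linear mixed models (LMM) for the PTSD measures and the secondary outcomes.

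On background care, *Treatment as usual* states: "TAU is considered to be equal in the three conditions as a result of the randomization procedure used".

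**The concern.** The protocol decides which measures serve the safety objective, and those measures do not cover everything it says clinicians are worried about. Elsewhere it treats exacerbation as a safety matter. The background supports the pilot studies by reporting neither serious adverse events nor symptom exacerbations, and the therapist burden scale asks whether PTSD and psychosis will get worse. In the trial itself, worsening in individual patients is not among the designated adverse-event outcomes.

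At stake is what a favourable safety statement would mean. A checklist showing no excess of admissions, crises or self-harm, together with improved mean symptom scores, could be offered to reluctant clinicians as evidence of safety. It would still leave open how many patients deteriorated, and whether more did so under treatment than on the waiting list. The sentence on usual care adds to this. Medication change is one of the feared consequences, and care received after allocation is presumed equal.

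**Working it through.** **1. Named harms against the adverse-event row.**

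| Harm named in *Clinical attitudes and practice* | T-AEQ item | Session ratings |
|---|---|---|
| Symptom exacerbation | none | partly (hearing voices), PE and EMDR only |
| Crisis | yes | not among the examples given |
| Hospitalisation | yes | not among the examples given |
| Self-harm | yes | not among the examples given |
| Suicidal behaviour | yes (attempt) | partly (being suicidal), PE and EMDR only |
| Rapid medication change | none | not among the examples given |

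The T-AEQ reaches 4 of 6.

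**2. Which measures allow a waiting-list comparison.** *Design* compares the three groups at T0, T2 and T6. *Measurements* confines within-session assessments to PE and EMDR. The T-AEQ therefore has a comparator at T0, T2 and T6, and the session ratings have none. CAPS, PSS-SR, AHRS, DRS, GPTS, BDI-II and TiC-P are all scheduled at T0, T2 and T6.

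**3. The evaluable sample.** The protocol gives 159 evaluable participants for a three-group F-test (alpha 0.05, power 0.80, medium effect). Taking medium as f = 0.25 (an assumption), the noncentral F distribution gives a minimum N of 158. Power at 159 is 0.805, so the figure reproduces. With 33% attrition, 159 / (1 − 0.33) = 237.3, rounded up to 238, and then to 3 × 80 = 240. Evaluable per arm: 159 / 3 = 53.

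**4. Why a mean can hide a minority (assumed figures).** Suppose that in a treated arm 15% worsen by 1 SD and 85% improve by 0.5 SD:

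mean change = 0.85 × 0.5 − 0.15 × 1.0 = 0.275 SD improvement.

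With 20% worsening: 0.80 × 0.5 − 0.20 × 1.0 = 0.20 SD improvement.

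These figures describe one arm. The LMM contrast favours treatment only if the waiting list improves by less than that on average, for example if it stays unchanged.

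**5. Precision of a comparison of worsening rates (assumed 15% versus 5%).**

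half-width = 1.96 × √(0.15 × 0.85/53 + 0.05 × 0.95/53) = 1.96 × √(0.175/53) = 0.113.

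With all 80 per arm: 1.96 × √(0.175/80) = 0.092.

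Power to detect a doubling (two-sided 0.05), over a range of assumed waiting-list rates:

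| Waiting list → treated | 53 per arm | 80 per arm |
|---|---|---|
| 5% → 10% | 16% | 22% |
| 10% → 20% | 30% | 42% |
| 20% → 40% | 62% | 79% |

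**The case against.** The strongest reply is that deterioration is measured. CAPS and PSS-SR are in the table captioned for PTSD and safety together, and they are compared with the waiting list. Psychosis against the waiting list is an explicit secondary objective, and depression is a secondary outcome. A treatment that made patients worse on average would be seen. This stands. A reader might infer that the trial cannot detect symptom worsening, or could declare safety without testing it at all; the documents do not support that. Nor do they support the inference that the omitted harms are the ones feared most. The list is unranked, the Discussion pairs deterioration with crisis, and the T-AEQ covers crisis.

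A second reply is that a worsening threshold and its analysis belong in an analysis plan, which is not shown. For the threshold that is right, and its absence is not held against the article. Which measures serve a primary objective is different: the article makes that choice in Table 1 and in describing the T-AEQ.

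Third, the usual-care sentence describes background care and does not mention safety. That also stands, so it is treated as a separate correction. A reader might infer that treating teams will know the allocation and adjust medication accordingly. The article says only that assessors are blind and does not describe what the teams know.

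Finally, the TiC-P is a costing list. Nothing shown establishes that it would register rapid changes of drug or dose.

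**Conclusion.** The point holds as one of coverage and linkage. The adverse-event row omits symptom exacerbation and rapid medication change, two of the six harms named, and one of its two instruments cannot inform a comparison with the waiting list. Data bearing on both omissions exist in all three arms at T0, T2 and T6. Except for CAPS and PSS-SR, which share the Table 1 caption, they are assigned to efficacy or costing, and the stated analysis of the scales is by means. The claim that the T-AEQ establishes safety is therefore too strong.

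This does not invalidate the design. It is an inexpensive improvement that should be made, because the safety conclusion is meant to influence practice. The mixture example rests on assumed rates and on an assumption about the waiting list, so it shows what could happen and does not predict it. The half-width of about 11 points rests on 53 evaluable per arm and assumed rates of 15% and 5%. Only large differences in worsening would be clearly visible.

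**What to change.** - Assign existing data to the safety objective. At T2 and T6, for PE and for EMDR versus waiting list, report the risk difference with 95% confidence interval for the proportion whose score worsened from T0 beyond one threshold per scale. Fix the thresholds before unblinding.
- Use CAPS for PTSD, with AHRS, DRS, GPTS and BDI-II as supporting scales, each reported separately and descriptively, without multiplicity claims.
- State that absence of a difference is not proof of safety, and give the expected interval width.
- Label the session ratings as description within treatment only.
- Replace the statement that the T-AEQ establishes safety with one saying that it records specified adverse events.
- Separately, reword the usual-care sentence: randomisation balances usual care at entry only. Compare usual care and medication use received by arm from the TiC-P, noting that this list may not capture rapid changes.

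The cost is wording and some tables. Five scales × two time points × two contrasts make 20 risk differences, most with wide intervals. No new instrument, visit or participant is needed.

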### Inclusion and exclusion

The criteria for inclusion in the intervention study are: a) age between 18 and 65 years; b) a lifetime history of a psychotic disorder or a mood disorder with psychotic features (M.I.N.I. plus); c) meeting DSM-IV-TR diagnostic criteria for PTSD (Clinician Administered PTSD Scale (CAPS)).

The criteria for exclusion are: a) high suicidality, operationalized as the combination of having a high suicidality score on the M.I.N.I. with the last suicide attempt within the past six months and a depression score on the Beck Depression Inventory-II (BDI-II) of 35 or higher; b) changes in medication (mood regulators, antipsychotics) within two months prior to the study; c) insufficient competence in the Dutch language; d) severe intellectual impairment, defined as an estimated IQ below 70 (mental retardation); e) not being able to travel to and from the place of assessment and therapy; and f) participant is in seclusion or admitted to a closed ward.

See Figure 1, the T.TIP flowchart. All mental health teams that signed up for cooperation in the T.TIP study carry out the standard procedure for screening of all patients suffering from psychosis. After that, the flow of consenting and screened participants into the study has three pathways: (1) ‘regular’ inclusion, meaning that each patient demonstrating a high risk for PTSD (TSQ ≥6) will be invited for an inclusion interview; (2) ‘low TSQ’ inclusion, meaning that a random sample of patients across the teams (N = 200) demonstrating a low risk of having a PTSD (TSQ ≤5) will be invited for a ‘low TSQ’-inclusion interview; and (3) ‘incidental referrals’-inclusion.

The inclusion interview conducted by the research assistant (RA) will be the same for all three categories ‘regular’, ‘low TSQ’ and ‘incidental referrals’: (a) three sections of the M.I.N.I.-Plus interview for assessing psychotic disorders, mood disorders with psychotic features and a risk analysis regarding acute suicidality; (b) the CAPS [61] for assessing a PTSD diagnosis; and (c) the BDI-II [62] for assessing the severity of depressive symptoms.

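### The between-arm safety comparison rests on patient self-report with no death item and no second source, while 33% attrition is planned for; events may be under-counted

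*Protocol article*

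**What the plan says.** The protocol article makes "the safety of PE versus waiting list and EMDR versus waiting list in the treatment of PTSD" part (b) of the primary objective. In the section on measuring PTSD symptoms and safety, it says that the T-AEQ "is a checklist that establishes treatment safety". The patient is the informant: "In seven questions the patient is asked to report any self-inflicted pain or injury, suicide attempt". The list ends with "having needed help because of a crisis and being admitted to a psychiatric hospital", and "The time frame is two months". Death is not among the seven items.

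Table 1 lists two adverse-event measures, both marked as self-report:
- The T-AEQ, at T0, T1, T2, T6 and T12.
- Session ratings, at treatment sessions 2 and 3. The waiting list has no sessions in this period, so these cannot enter a comparison between arms.

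The TiC-P also asks about hospital stay. It is self-report in Table 2 and serves the cost analysis.

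On missing data, the power section states: "Attrition is estimated conservatively to be high at 33" per cent. The paragraph on minimising missing values (after Figure 1) has research assistants contact "case workers for inviting participants and for reminding them about their assessment appointments". It also pays for each measurement at T0, T2, T6 and T12 whether or not the participant stays in treatment. Case workers are not named as a source of outcome data.

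**The concern.** A self-report checklist records an event only if the patient answers it. Several listed events (suicide attempt, crisis, psychiatric admission) could plausibly make a patient less likely to answer, and a death can never be self-reported. If non-response is related to having had an event, the rate among responders is not the rate among those randomised. If the amount of non-response, or its link to events, differs by arm, the comparison with waiting list is distorted as well. The mixed model in the Analyses section is specified for the PTSD and secondary outcomes; a model of scale scores does not recover events that nobody reported.

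The article's Discussion presents a finding of safety as a main contribution that would support use of these treatments in practice. A result that cannot be told apart from under-ascertainment would be weak ground for that.

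**Working it through.** **The plan's own figures.** The power section gives an F-test over three groups, alpha 0.05, power 0.80, a medium effect, 159 participants, 33% attrition and 3 × 80 = 240. Taking medium as f = 0.25 (not printed), the noncentral F gives N = 158, or 159 in equal groups (power 0.805). Inflating, 159/(1 − 0.33) = 237.3, so 238; the plan's 240 is consistent. No event rate and no power for safety are stated.

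**Reports per arm.** 80 × 0.33 = 26.4, so about 26 patients per arm without a report and 54 with one.

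**Bounds with no assumption about the mechanism.** Suppose 5% of the 54 responders report an event (0.05 × 54 = 2.7, an illustrative rate).
- No missing patient had an event: 2.7/80 = 3.4%.
- Every missing patient had one: (2.7 + 26)/80 = 35.9%.
- With 20% missing (16 of 80) the range is 4.0% to 24.0%; with 10% missing (8 of 80) it is 4.5% to 14.5%.

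**Rate among responders if missingness is linked to events.** Let p be the true rate, m overall missingness, and R the ratio of missingness in patients with an event to that in patients without. Then m0 = m/(1 − p + pR), m1 = R·m0, and the observed rate is p(1 − m1)/(1 − m). The values of p and R are assumptions, since the article gives neither.

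For p = 10%, m = 33%, R = 2: m0 = 0.33/1.1 = 0.30, m1 = 0.60, observed = 0.1 × 0.4/0.67 = 6.0%.

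| True 10%, m = 33% | R = 0.5 | R = 1 | R = 1.5 | R = 2 | R = 2.5 |
|---|---|---|---|---|---|
| Observed | 12.3% | 10.0% | 7.9% | 6.0% | 4.2% |

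At R = 2 and m = 33%, a true 5% is seen as 2.8% and a true 20% as 13.4%. With less missingness the effect shrinks: for a true 10% and R = 2, 8.0% is seen at m = 20% and 9.1% at m = 10%.

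**Difference between arms.** Take a true 10% in both arms and R = 2.
- 33% missing in a treated arm, 15% on the waiting list: 6.0% versus 8.6% (for 15%: m0 = 0.15/1.1 = 0.136, m1 = 0.273, 0.1 × 0.727/0.85 = 8.6%).
- Missingness reversed: 8.6% versus 6.0%.
- Equal missingness of 33%: 6.0% in both.

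Now take true rates of 20% and 10%, with 60% missing after an event and 30% otherwise in both arms.
- Observed rates: 0.2 × 0.4/(0.2 × 0.4 + 0.8 × 0.7) = 0.08/0.64 = 12.5%, and 0.04/0.67 = 6.0%.
- True odds ratio: (0.2/0.8)/(0.1/0.9) = 2.25. Observed: (0.08/0.56)/(0.04/0.63) = 2.25.
- The odds ratio is preserved; the absolute difference falls from 10 to 6.5 points.

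**The case against.** Much of the case on the other side stands.

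- **Entry criteria.** A reader might infer from the exclusion for "not being able to travel to and from the place of assessment and therapy", and from the closed-ward exclusion, that a patient admitted during the trial cannot be assessed. Those criteria govern entry and say nothing about follow-up. A patient discharged before the visit can still report an admission within the two-month window.
- **Retention measures.** Assessments are paid for after treatment dropout, with letters, texts, calls and case-worker contact. The 33% is a deliberately high sample-size allowance and is not tied to adverse events. At T1 the therapist hands out the questionnaires, so not every report needs a research visit.
- **Direction of bias.** A reader might conclude that the rates are biased downwards and that a finding of safety is to be expected even if false. The article gives no event rates and no reasons for missingness. At a ratio of 1 there is no bias, and below 1 the rate is overstated. Shrinking a true 10-point excess to 2.5 points (12.5% versus 10%) needs the event link to hold in a treated arm only, which nothing in the article supports.
- **What may stand elsewhere.** Reporting of serious adverse events and deaths, and the safety analysis, may sit in the full protocol or SAP. Silence in the article does not show that such events go uncounted.

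What survives is what the article does fix. It names one instrument as establishing safety, with the patient as informant, no death item and a schedule that depends on response. Reminders and payment reduce non-response but cannot capture a death.

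**Conclusion.** The point holds in conditional form. The comparison with waiting list on a primary objective depends on patient reports alone, and the plan allows for about 26 of 80 patients per arm without one. Under-counting follows if, and only if, patients with events respond less often than others. Its size rests on assumed ratios: at 33% missing, a true 10% is seen as 7.9% at ratio 1.5, 6.0% at ratio 2 and 4.2% at ratio 2.5. Bias in the difference between arms can have either sign, and the odds ratio is unaffected when the same missingness pattern holds in both arms. The bounds of 3.4% to 35.9% assume nothing about the mechanism, only that the planned 33% attrition occurs; an interval that wide could not support a conclusion of safety. The documents do not show that the trial will under-report harm. They show that this design could not rule it out, and that a second source would improve on it at low cost.

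**What to change.** Keep the full T-AEQ as planned. Add, for every randomised participant in all three arms and whether or not they attend or stay in therapy, case-worker or chart information on death, psychiatric admission, crisis contact, and known suicide attempt or self-injury. Collect it at T2 and T6, and at T12 for PE and EMDR, in the same way in every arm. Count an event if either source shows it, so that attempts unknown to services but reported by the patient are not lost. Base the safety comparison on all randomised participants.

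Existing trial staff who do not rate the CAPS should do this. Charts and case workers may reveal the allocation, and the blinded research assistants should not be exposed to it.

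If the look-back runs to the previous time point, this also covers a gap that exists even with full attendance. With T2 and T6 at months 2 and 6, a two-month recall window leaves months 2 to 4 unasked.

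The cost is consent wording for case-worker or chart information and modest extra data collection, since present contact with case workers covers only invitations and reminders. Charts may under-record minor events, which is why self-report stays.
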